### Cytological assessment

Samples will be centrifuged at 3000 revolutions per minute (RPM) for 5 min, supernatant decanted and the pellet resuspended in 6 mL BD CytoRich Red Preservative. After 1 hour, the fixed sample will be centrifuged at 1500 RPM for 10 min, supernatant decanted and the remaining pellet prepared into a liquid-based cytology Papanicolaou stained slide using the BD PrepStain (Becton Dickinson UK) according to the manufacturer’s instructions. The stained slide will be dehydrated in two changes of industrial methylated spirits, cleared in two changes of xylene and cover-slipped. Two observers, a consultant cytopathologist and a consultant biomedical scientist, will review each slide independently and record their results. A second consultant cytopathologist will review any discrepant cases, which will be settled by consensus review at a multiheaded microscope. Final cytology results will be logged under the unique study ID on the study database. intraobserver and interobserver variability will be determined by blinded, independent review of a random selection of anonymised test positive, test negative, complex and discrepant cases at the end of the study and reported separately.

### Classification of cytology results

Cytology slides will be reported according to the classification system shown in table 1. For the primary analysis, atypical cells of uncertain significance (ACUS), suspicious, adenocarcinoma or malignant (other) cytology results will be considered positive. Glandular cells and no malignant cells seen will be considered negative. Unsatisfactory results will not be classified as either positive or negative, and the participant will be invited to provide a second sample for cytological analysis. Secondary analysis will include cancers of other pelvic sites (cervix, vagina, uterus, ovary, fallopian tube, bladder, kidney or bowel). Sensitivity analysis will consider the diagnostic performance of positive urogenital cytology that includes glandular results as potentially malignant findings.

**Table 1 T1:** Cytological classification

Cytology result	Cytological findings	Primary analysis	Sensitivity analysis
Unsatisfactory*	Sample obscured by debris, lymphocytes or bacteria	Indeterminate	Indeterminate
NMCS	No malignant cells seen	Negative	Negative
Glandular cells	Endometrial glandular cells seen	Negative	Positive
ACUS	Atypical cells of uncertain significance	Positive	Positive
Suspicious	Atypical glandular cells, suspicious for malignancy	Positive	Positive
Adenocarcinoma	Adenocarcinoma malignant cells seen	Positive	Positive
Malignant (others)	Malignant cells of non-endometrial origin	Positive	Positive

*Urine according to the Paris criteria.

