### Index tests

The timing of urine and vaginal sampling is important to ensure validity of the results. Both research samples will be taken before any routine clinical procedures to avoid inadvertent contamination with iatrogenically dislodged endometrial cells (study schema, figure 1). Of the two research samples, urine will be collected first because vaginal sampling will remove naturally shed uterine debris from the lower genital tract and affect interpretation of the results.

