### Urine samples

Using both written and verbal instructions, we will ask women to bring to clinic a first catch sample of their first urinary void of the day, collected in a sterile pot. A second voided urine sample will be collected by the participant on arrival at the clinic, before any other research or clinical procedures are carried out. This will ensure that every woman has at least one satisfactory urine sample available for analysis.

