### Sample handling

Urine samples will be tested for haematuria by dipstick. Urine and vaginal samples will be fixed with equal volumes of BD CytoRich Red Preservative (Becton, Dickinson and Company, the USA) to preserve cellular integrity, prevent degradation and inhibit bacterial overgrowth. Samples will be sent to the Manchester Cytology Centre at the Manchester University NHS Foundation Trust (MFT). Samples will be anonymised and labelled with sample type (urine or vaginal fluid) and a unique study identifier (study ID) to prevent accidental unblinding of the cytopathology team. With the exception of whether the participant is taking exogenous hormones, all clinical data will be withheld from the cytology team until consensus results are received. Second urine samples will be fixed with BD CytoRich Red Preservative and stored at 4°C until the first urine sample has undergone cytological assessment. This second sample will undergo cytological review if the first urine sample is inadequate for analysis or post hoc, if the first urine sample is false negative for endometrial cancer detection. Residual samples will be stored in the MFT Biobank for future biomarker discovery work. Samples will be either embedded in agar cell blocks to preserve cellular integrity for future immunocytochemistry or centrifuged to pellet the cellular material. The resulting pellet plus aliquots of the supernatant will be stored at −80°C.

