### Blinding

In most cases, research samples will be collected prior to routine diagnostic workup, and sample takers will be blinded to participant cancer outcomes. If the proportion of cases is less than 5% at the midpoint of the study, the cohort will be enriched with endometrial cancer diagnoses by recruiting higher-risk women (endometrial thickness >4 mm on TVS) and those with proven endometrial cancer prior to hysterectomy. Care will be taken to collect research samples at least 7 days after any diagnostic uterine instrumentation. The cytology team will always be blinded to the cancer status of participants when performing cytological review of urine and vaginal samples. They will have no access to clinical data or results of routine diagnostic tests. Individual participants will not routinely receive their cytology results.

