### Handling of discordant results

The accuracy of urogenital cytology will be measured against standard diagnostic tests for endometrial cancer. Concordance of cytology results between observers will be recorded, but primary analysis will consider ‘ACUS’, ‘suspicious’, ‘adenocarcinoma’ or ‘malignant (others)’ cytology results by consensus opinion to be a positive result. ‘False negative’ results, where standard tests identify endometrial cancer but urogenital cytology does not, will be reviewed to identify possible contributing factors (patient factors, tumour factors or test errors). Subject to ongoing consent, women will be resampled before they undergo hysterectomy, to determine whether repeat sampling is helpful for missed cases. This will be possible because cytology results will be reported prospectively, in ‘real time’ and on a weekly basis, wherever possible. Cytology review of missed cases will be carried out at a multiheaded microscope by the cytology team. Second±further slides will be prepared and reviewed where sufficient residual sample allows. ‘False positive’ cases, where urogenital cytology is positive but standard tests are not, will be handled carefully. If the diagnostic pathway (figure 2) has not been completed, the responsible clinician will be contacted and asked to consider further tests, for example, hysteroscopy or an MRI scan. If the malignant cells identified by cytology could have originated elsewhere, further tests may be warranted (eg, cystoscopy and colposcopy). Retrospective blinded review of 10% of cases, including test positive, test negative, complex and discrepant cases, will facilitate formal assessment of intraobserver and interobserver variability and whether or not there is evidence for a ‘learning curve’ effect.

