Analysis of the primary objective will compare the clinical performance of cytology with the reference test. Thus, sensitivity, specificity, NPV, positive predictive value and diagnostic accuracy will be reported together with their corresponding 95% CIs, calculated using the exact binomial method. Where a histology result is not available, endometrial thickness <4 mm (histology not indicated) or discharge from diagnostic workup will be used as reference standard. Analysis of the secondary objectives will assess clinical performance of the urine test alone and the vaginal test alone for the detection of endometrial cancer in relation to the reference test. The clinical performance of urine and vaginal cytology for the detection of any cancer affecting the pelvic organs will also be calculated. Secondary analyses will follow the same approach as the primary analysis. Sensitivity analyses will consider the clinical performance of cytology with a broader definition of a positive cytology result (including glandular results as test positives). Interobserver agreement between the cytopathologists will be assessed using the kappa statistic and categorised as poor, fair, moderate and good. McNemar’s χ^2^ test will be used to compare urogenital cytology with routine diagnostics. Multivariate logistic regression will evaluate the relationship between positive cytology and endometrial cancer diagnosis while adjusting for potentially predictive clinical characteristics like age and BMI. The diagnostic accuracy of urogenital cytology will be compared with individual elements of the standard diagnostic pathway, including TVS, hysteroscopy and endometrial biopsy. Consideration will be given as to where in the current diagnostic pathway for endometrial cancer urogenital cytology fits. Its use as a triage test prior to any other diagnostic workup both alone and in combination with clinical parameters (eg, age and BMI) will be modelled. We will also consider its usefulness in combination with transvaginal ultrasound scanning at various endometrial thickness cut-offs. The acceptability of urogenital sampling will be compared with transvaginal ultrasound, hysteroscopy and endometrial biopsy (online supplemental appendix 1).

10.1136/bmjopen-2021-050755.supp1Supplementary data

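### Unsatisfactory cytology is set aside in every stated analysis, and an invited repeat vaginal sample is not reconciled with the rule that samples precede clinical procedures

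*Protocol article*

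**What the plan says.** **Unsatisfactory results.** Classification of cytology results states: "Unsatisfactory results will not be classified as either positive or negative, and the participant will be invited to provide a second sample". Table 1 describes the category as "Sample obscured by debris, lymphocytes or bacteria" and assigns it to indeterminate under both the primary and the sensitivity analysis. The only sensitivity analysis described for cytology concerns glandular cells. Statistical analyses puts it this way: "Sensitivity analyses will consider the clinical performance of cytology with a broader definition of a positive cytology result". It does not touch unsatisfactory results.

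**Definition of accuracy.** Primary outcome measure takes sensitivity as a proportion of women with endometrial cancer and specificity as a proportion of women without it. Neither definition is restricted to women with a readable sample.

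**Timing of samples.** Index tests requires: "Both research samples will be taken before any routine clinical procedures to avoid inadvertent contamination with iatrogenically dislodged endometrial cells". For urine there is a reserve. Urine samples says: "A second voided urine sample will be collected by the participant on arrival at the clinic, before any other research or clinical procedures". Sample handling adds: "This second sample will undergo cytological review if the first urine sample is inadequate for analysis". No equivalent reserve is described for the vaginal sample. Handling of discordant results says that cytology is reported "on a weekly basis, wherever possible". Blinding says: "Care will be taken to collect research samples at least 7 days after any diagnostic uterine instrumentation". That sentence follows directly on the plan to enrich the cohort with higher-risk women and proven cancers.

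**The concern.** Two questions arise from the same rule.

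1. Cytology is proposed as a triage test that would let negative women be reassured without invasive tests. A sample that cannot be read reassures nobody. If unreadable results leave the calculation in every stated analysis, the published sensitivity and specificity describe readable samples, not the test as offered to all women with postmenopausal bleeding.

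2. The replacement matters as well. A repeat vaginal sample requested after the cytology report comes later than the sampling visit. If biopsy or hysteroscopy has taken place in between, the repeat may contain the dislodged cells that the sampling rule is meant to keep out. In a woman with cancer, that could turn an unreadable test into a positive one. Almost every woman with cancer will have been instrumented, because a positive reference result in the primary analysis rests on histology. The abstract ties the sample size to the sensitivity of vaginal samples, which is the sample type without a reserve.

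**Working it through.** **Step 1. The plan's own figures.** Inputs from Sample size: about 2000 women, 5% prevalence (100 with cancer, 1900 without), 85% sensitivity and specificity, margins of 7 and 2 points, about 1630 negative tests, NPV 99.1%. They reproduce as a precision calculation:

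- Cancers needed: 1.96² × 0.85 × 0.15 / 0.07² = 99.96; divided by 0.05, this gives 1999 women.
- Half-widths: 1.96 × √(0.1275/100) = 7.0 points; 1.96 × √(0.1275/1900) = 1.6 points.
- Negatives: 0.15 × 100 + 0.85 × 1900 = 15 + 1615 = 1630; NPV = 1615/1630 = 99.1%.

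These figures make no allowance for women without a usable result.

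**Step 2. Women with no usable result.** The article gives no rate. Assume a share u, equal in women with and without cancer, and 85% correct among readable tests. Sensitivity is then:

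- set aside: 0.85 for any u;
- counted as missed (negative): 0.85 × (1 − u);
- counted as positive: 0.85 × (1 − u) + u.

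The half-width, when results are set aside, is 1.96 × √(0.1275 / [100(1 − u)]).

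| u (assumed) | Set aside | Counted as missed | Counted as positive | Half-width, set aside |
|---|---|---|---|---|
| 2% | 85.0% | 83.3% | 85.3% | 7.07 points |
| 5% | 85.0% | 80.8% | 85.8% | 7.18 points |
| 10% | 85.0% | 76.5% | 86.5% | 7.38 points |

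Specificity mirrors this: 83.3%, 80.8% and 76.5% if failures count as positive; 85.3%, 85.8% and 86.5% if they count as negative.

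**Step 3. The combined test.** Step 2 applies directly to a single-sample analysis, or to women with no readable sample at all. If one readable sample of either type suffices, far fewer women are lost. With 10% failure per sample and independence (both assumed):

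- vaginal sample and one urine both fail: 0.10² = 1%, so counting these as missed costs 0.85 points of sensitivity;
- vaginal sample and both urines fail: 0.10³ = 0.1%, which costs about 0.1 point.

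The article does not say how a woman with one satisfactory and one unsatisfactory sample is classified, so neither figure can be confirmed.

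**Step 4. Replacement by a repeat.** If every unsatisfactory sample in women with cancer is replaced by a repeat with sensitivity r, the reported value is 0.85 × (1 − u) + r × u. With r = 0.85 it stays at 85.0%. With r = 1, the extreme of contamination, it is 85.3%, 85.8% and 86.5% for u of 2%, 5% and 10%: an addition of 0.3 to 1.5 points.

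**Step 5. Timing, by sample type.**

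- *Urine.* The reserve is collected on arrival, before any procedure, and is read if the first sample is inadequate. This agrees with Index tests.
- *Vaginal.* A repeat follows an invitation, which follows a report issued about weekly. Under Clinical diagnostic pathway, all women have an ultrasound scan and those at or above 4 mm have a biopsy. The repeat may therefore come after instrumentation. The article does not say whether such a repeat enters the primary analysis, or whether the 7-day interval applies to it.

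**The case against.** The strongest case against has four parts.

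- **The urine reserve already solves the problem for one of the two samples.** This stands in full.

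- **Inflation is not shown.** A reader might infer that setting unreadable results aside inflates accuracy. Step 2 shows that this depends on the class assigned to them. If unreadable women are referred, sensitivity rises. Coding all failures one way cannot lower both measures: negative lowers sensitivity and raises specificity, and positive does the reverse. Both fall only on a literal reading of the outcome definitions, where an unreadable test is in neither numerator. That reading is defensible, but it is a convention and not a demonstrated bias. The rate, and whether failure is related to cancer, are also unknown.

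- **A reader might infer that repeats will usually follow instrumentation and so break the study's own rule.** The documents do not support this. Women below 4 mm need no biopsy and their share is not given. The article does not say that biopsy takes place at the sampling visit. Blinding also says only that samples precede workup in most cases, and its 7-day sentence is worded generally. What remains is that the interval's scope over repeats is unclear, and that women with cancer are the ones most likely to have been instrumented.

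- **Some of this may be planned elsewhere.** The article promises a STARD diagram and a table of the index test against the reference standard, and an analysis plan not shown may hold further analyses. That tempers the point but does not remove it, because Table 1 states the handling as a rule for both analyses.

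**Conclusion.** The point holds in a limited form. Every stated accuracy estimate is conditional on a readable sample, while the primary outcome is defined over all women. The timing of a repeat vaginal sample is not reconciled with Index tests or tied to the interval in Blinding. Urine is not affected by the timing problem.

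The size cannot be fixed from the documents. On assumed rates of 2% to 10% with no usable result, equal in both groups and with 85% correct among readable tests, setting failures aside reports a sensitivity 1.7 to 8.5 points above the value that counts them as missed, and 0.3 to 1.5 points below the value that counts them as positive. The upper end exceeds the 7-point margin, but it requires that no reserve, repeat or second sample type rescues the woman. For the combined test the effect may be below 1 point. The two effects should not be added, since a woman with an adequate repeat is no longer without a result.

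**What to change.** 1. Base the primary analysis on the first adequate sample taken before any uterine instrumentation, including the stored second urine. Report repeat vaginal samples taken after instrumentation separately. The enrichment cohort stays under the terms in Blinding.
2. State how the combined test is classified when one sample is satisfactory and the other is not.
3. Add a sensitivity analysis that keeps women with no adequate sample in the denominators, counting them first as test negative and then as test positive.
4. Report the unsatisfactory rate by sample type and by disease status.
5. Reconcile Classification of cytology results, Index tests and Blinding on the timing of repeat vaginal samples, and say whether the interval in Blinding covers them.

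The cost is some wording, a little more analysis, and figures that may be slightly less favourable or have wider intervals.

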### Clinical diagnostic pathway

Women will be investigated by TVS, outpatient hysteroscopy and/or endometrial biopsy according to local clinical diagnostic pathways for the investigation of PMB (figure 2).^3^ All women will have their endometrium measured by TVS. Those with an endometrial thickness <4 mm will be considered at low risk of endometrial cancer and alternative diagnoses explored. Women with ≥4 mm endometrial thickness will undergo an endometrial biopsy using a pipelle endometrial sampler. Those with an irregular thickened endometrium, where focal pathology is visualised or suspected, will have an outpatient hysteroscopy and suspicious lesions biopsied under direct vision. Hysteroscopy will be performed under general anaesthesia where outpatient hysteroscopy fails, biopsies are inadequate for diagnostic purposes or uterine instrumentation is poorly tolerated. Endometrial polyps will be resected to allow full histological interpretation. Tissue samples will be formalin-fixed, paraffin-embedded, cut into 4 µm sections, stained with H&E and cover-slipped as per routine practice. At least one pathologist will review all biopsies; suspicious or abnormal biopsies will be reviewed by two specialist gynaecological pathologists at the cancer centre (St Mary’s Hospital) as per routine clinical practice; difficult cases will be reviewed by additional specialist members of the gynaecological pathology team. Hysterectomy specimens will be fixed, cut, sectioned and reviewed according to the International Federation of Gynecology and Obstetrics (FIGO) 2009 staging criteria (endometrial cancer) and the WHO classification system (atypical hyperplasia).^17 18^

**Figure 2 F2:**
[figure not shown]
Diagnostic pathway for women referred to secondary care for the urgent investigation of unexplained postmenopausal bleeding (PMB).

### Reference standard

The reference standard is histology where endometrial tissue is collected for routine diagnostic and staging purposes. The hysterectomy specimen will be used in preference to the endometrial biopsy, where available within 3 months of endometrial biopsy and where there was no treatment with neoadjuvant chemotherapy or hormone therapy. Histology results will be classified as inadequate, benign, atypical hyperplasia and endometrial cancer (of any histological subtype or grade). For the primary analysis, a histological diagnosis of endometrial cancer will be considered a positive result. We will report overall results as well as a breakdown by histological subtype and stage of disease. Hyperplasia and benign endometrium will be considered a negative result. In secondary analyses, cancers of other pelvic sites (cervix, vagina, uterus, ovary, fallopian tube, bladder, kidney or bowel) will be considered a positive result. We will record cases of atypical hyperplasia and their cytological interpretation. In cases where an endometrial biopsy is not indicated (endometrial thickness <4 mm and/or normal hysteroscopy) or fails (inadequate sample), the reference standard will be discharge from diagnostic workup. Passive clinical follow-up of negative women will ensure missed diagnoses of endometrial cancer are minimised. This will involve monitoring for any subsequent rereferrals to our service. A diagnosis of endometrial cancer within 3 months of initial discharge from diagnostic workup will be considered a positive clinical result.

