### Outcome measures

#### Primary outcome measure

*Sensitivity*—the proportion of women with endometrial cancer who test positive by cytology (true positive rate) and *specificity*—the proportion of women who do not have endometrial cancer who test negative by cytology (true negative rate). The accuracy of cytology (index test) will be defined by the results of standard endometrial cancer diagnostic tests (reference standard, figure 2).

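### Discharge counts as no cancer for women with ≥4 mm and no adequate histology even if the pathway was not completed, and only positive cytology prompts its completion, so sensitivity and NPV may be modestly overstated

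*Protocol article*

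**What the plan says.** All places are in the Methods of the protocol article.

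- **Clinical diagnostic pathway.** All women have a transvaginal scan. "Women with ≥4 mm endometrial thickness will undergo an endometrial biopsy using a pipelle endometrial sampler". For difficult cases there is a further step: "Hysteroscopy will be performed under general anaesthesia where outpatient hysteroscopy fails, biopsies are inadequate for diagnostic purposes or uterine instrumentation is poorly tolerated".
- **Reference standard.** Histology is used where tissue is obtained. Where biopsy is not indicated (thin endometrium and/or normal hysteroscopy) "or fails (inadequate sample), the reference standard will be discharge from diagnostic workup". Women classed negative are followed passively: "This will involve monitoring for any subsequent rereferrals to our service". One rule can overturn the negative label: "A diagnosis of endometrial cancer within 3 months of initial discharge from diagnostic workup will be considered a positive clinical result".
- **Statistical analyses.** For any woman without a histology result, either a thickness below 4 mm or discharge from workup serves as the reference.
- **Primary outcome measure.** The accuracy of cytology "will be defined by the results of standard endometrial cancer diagnostic tests (reference standard, figure 2").
- **Handling of discordant results.** Cytology is reported weekly where possible, while the study runs. False positive cases, "where urogenital cytology is positive but standard tests are not, will be handled carefully". For these, if the pathway "has not been completed, the responsible clinician will be contacted and asked to consider further tests". No matching contact is described for cytology-negative women. The review and resampling of false negatives concerns only cancers that the standard tests have already found.

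**The concern.** Two rules act together. The classification rule turns discharge into a negative reference result without asking whether the steps due at 4 mm or more were done. The prompt rule then makes the chasing of an incomplete workup depend on the index test. A cytology-positive woman with an incomplete pathway may be sent for more tests, so her cancer can be found and counted as a true positive. A cytology-negative woman in the same position gets no such prompt. She is counted as a true negative unless cancer is diagnosed within 3 months.

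This is verification that depends on the test being evaluated. Blinding the cytologists does not prevent it, because the influence runs from the cytology report to the workup. Sensitivity is a primary outcome, and together with NPV it carries the rule-out use described in the Introduction. The confidence intervals would not reflect a bias of this kind.

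**Working it through.** **The plan's own figures (Sample size section).** With 2000 women and 5% prevalence there are 100 cancers and 1900 women without. At 85% sensitivity and specificity: TP 85, FN 15, TN 1615, FP 285.

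- Half-width for sensitivity: 1.96 × √(0.85 × 0.15 / 100) = 0.070, the stated ±7%.
- NPV: 1615 / (1615 + 15) = 1615 / 1630 = 99.08%, Wilson 95% interval 98.49% to 99.44%, matching the stated 99.1% (98.5% to 99.4%).

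Both reproduce. They serve below as the table the study would report.

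**Assumptions (not in the documents).** 40% to 60% of women (800 to 1200) have ≥4 mm. All 100 known cancers are among them. Unverified women carry the same cancer risk as verified women with ≥4 mm and the same cytology result.

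**Scenario 1: the prompt is half effective.** Let f and g be the shares of cytology-negative and cytology-positive women with ≥4 mm left incomplete. True sensitivity = [85/(1−g)] / [85/(1−g) + 15/(1−f)].

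- f = 5%, g = 2.5%: 87.18 / (87.18 + 15.79) = 84.7%, so the reported 85% is 0.3 points too high. True NPV = 1 − 15.79/1630 = 99.03%.
- f = 15%, g = 7.5%: 91.89 / (91.89 + 17.65) = 83.9%, 1.1 points too high. True NPV = 1 − 17.65/1630 = 98.92%.
- f = g: 85.0%, no bias in sensitivity.

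**Scenario 2, the extreme: every unverified woman is cytology-negative.** This means the prompt resolves every cytology-positive case. Cytology-negative women with ≥4 mm number 15 + 0.85 × 700 = 610 (if 800 have ≥4 mm) or 15 + 0.85 × 1100 = 950 (if 1200). Let N, the unverified, be 5% or 15% of all women with ≥4 mm.

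| Women ≥4 mm | N | Risk in verified cytology-negative women | Hidden cancers |
|---|---|---|---|
| 800 | 40 | 15/570 = 2.63% | 1.05 |
| 800 | 120 | 15/490 = 3.06% | 3.67 |
| 1200 | 60 | 15/890 = 1.69% | 1.01 |
| 1200 | 180 | 15/770 = 1.95% | 3.51 |

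True sensitivity runs from 85/101.01 = 84.2% to 85/103.67 = 82.0%. True NPV runs from 1 − 16.01/1630 = 99.02% to 1 − 18.67/1630 = 98.85%.

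**Effect of the 3-month rule.** If it finds half of the 3.67 hidden cancers, reported sensitivity is 85/101.84 = 83.5% against a true 82.0%. The bias halves from about 3 to about 1.5 points.

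**The case against.** The strongest case against is that discharge from workup naturally means the end of the pathway described just before it. That pathway sends inadequate biopsies on to hysteroscopy under general anaesthesia, and the primary outcome ties the reference standard to figure 2, which is not shown here. What remains is refusals, failed instrumentation and deviations, and no design can force histology in those women. The 3-month check applies whatever the cytology result. If the cohort is enriched with proven cancers (Blinding section), those are already verified and dilute the effect. Finally, rules for missing reference results are often left to a full protocol or analysis plan.

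Much of this stands, and it limits the size. A reader might infer that every woman with a failed biopsy is discharged untested and called negative; the pathway section contradicts that. A reader might also infer that the bias could use up the planned ±7%. That would take 9 hidden cytology-negative cancers (85/109 = 78.0%), and nothing in the documents makes that number likely.

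The objection does not remove the point. The article itself provides for incomplete pathways, and the prompt it adds is for cytology-positive women only. The classification of women without histology is stated here, so it is not a detail deferred elsewhere. The 3-month check is passive, short and described through re-referrals to the study's own service, so it reduces the bias without removing it. Two uncertainties remain. The prompt may also cover workups still in progress, and it asks clinicians only to consider further tests, so its effect on verification may be partial.

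**Conclusion.** The point holds for a confined group: women with ≥4 mm, no adequate histology and a pathway that stayed incomplete. If cytology-negative women are left incomplete more often than cytology-positive women, reported sensitivity and NPV are too high.

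The size is unknown, because the documents give neither the share of women with ≥4 mm nor the share left unverified. Under the stated assumptions the overstatement of sensitivity is about 0.3 to 1.1 points with a half-effective prompt and up to 3 points at the extreme. NPV moves by at most about 0.2 points (99.08% to 98.85%), which stays inside the planned interval. If completion does not depend on cytology, sensitivity is not biased. The documents do not support a claim that the primary result is invalid; they support a modest bias in the test's favour that is cheap to limit and to show. The change should be made on that basis.

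**What to change.** 1. **Reference standard and Statistical analyses.** Accept discharge as reference-negative only for a thickness below 4 mm or after a completed pathway. State that a normal hysteroscopy counts as completion, as the Reference standard section already implies.
2. **Reporting.** Label the remaining women reference-indeterminate and show them by cytology result in the planned STARD diagram.
3. **Analysis.** Keep the current coding and add one sensitivity analysis that assigns these women the cancer risk of verified women with ≥4 mm and the same cytology result. State that equal risk is an assumption.
4. **Handling of discordant results.** Where feasible, apply the contact about an incomplete pathway to all women with ≥4 mm and no adequate histology, whatever their cytology. These steps are already routine care.

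Simply excluding the indeterminate women is not a remedy. In Scenario 2 it leaves sensitivity at 85/100 and removes mostly genuine true negatives, taking specificity to between 1575/1860 = 84.7% and 1435/1720 = 83.4%.

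The cost is some wording, one further analysis using routine workup and cytology results, and some extra clinician contacts. Sensitivity and NPV may come out slightly less favourable.
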